### Subgroup analyses

Subgroup analyses are the same in both the PNUD and sequential trials design. The authors of CF-WISE were careful in their conclusions, suggesting not all people with CF should discontinue ICS, including those with asthma for which ICS is an established treatment.^12^ In the trial, there was an imbalance in atopic status, with a higher rate in the ICS continuer arm. We will investigate discontinuation effects by asthmatic status, in addition to age (<18 and ≥18 years), baseline lung function (40–70 and >70 FEV_1_% predicted), *P. aeruginosa* infection status, inhaled bronchodilator use (ICS only vs ICS in combination with bronchodilator), provided sample size allows.

### Sensitivity analyses

Sensitivity analyses are planned to be the same in both the PNUD and sequential trials design. We will consider undertaking quantitative bias analysis (QBA) to quantify the potential impact of unmeasured confounding. QBA is an important set of tools for sensitivity analyses that test assumptions and impact of potential biases. One such technique is to use the strength of association between a confounder and outcome among unexposed, the strength of association between the confounder and treatment in the source population and the prevalence of the confounder as bias parameters.^39^

Robustness of results to the definition of the outcome will be assessed using an alternative definition for pulmonary exacerbation, restricting to hospital intravenous antibiotic use (excluding home use) and separately excluding intravenous episodes recorded as ‘planned’.

To address the potential for misclassification or failure to obtain accurate start and stop dates in the UKCFR, we will consider an alternative approach to the study design where an annualised definition of ICS discontinuation collected at annual review (whether the participant has stopped ICS since previous annual review) will be used.

### Missing data

Missing data in covariates will be summarised overall and by treatment status. Patterns of missingness over time will be explored and, based on likely missing data mechanisms, appropriate methods for handling missing data, such as inverse probability weighting and multiple imputation by chained equations, will be considered.^40^

### Patient and public involvement

The James Lind Alliance CF priority setting partnership identified the question ‘What are the effective ways of simplifying the treatment burden of people with CF?’ as a top research priority.^41^ This study addresses this priority by benchmarking an existing RCT and evaluating methods which may be appropriate to inform clinical decision making in an era where discontinuation of long-term treatments in CF is highly topical for the community.

As part of a wider project on TTE in CF, we will work in partnership with people with CF and members of the community through focus group sessions and manuscript review to guide the conduct and dissemination of this study.

### Benchmarking

#### Benchmarking the index trial

Benchmarking is the process for assessing compatibility between the results from a TTE using observational data and an index trial.^42^,^45^ We propose prespecified benchmarking criteria suggested by Wang *et al*,^45^ as follows:

Point estimates: Is the direction of the estimated HRs consistent between the trial and the target trial emulation? In addition, do the estimated effects of the emulated trial lie within the 95% CI of CF-WISE? This will be assessed quantitatively by calculating the standardised difference estimate and 95% CI for the difference using bootstrapping.^45^Clinical conclusion: Would the same clinical decision be made based on both the RCT and target trial emulation findings?

The assessment of these two criteria will be made in the context of the achieved harmonisation between the protocol of the index trial, target trial and observational emulation, with particular consideration to the alignment of study populations and causal questions.

#### Comparison of methods

The PNUD and sequential trials design were recently compared under the target trial framework and questions remain around the estimands they target, their suitability to discontinuation questions and model precision in smaller samples.^20^ In addition to benchmarking with CF-WISE, we will compare the point estimates and 95% CIs obtained under both designs. Discussion and exploration of comparisons between the two study designs will also be undertaken, namely with respect to causal estimands, eligibility and cohort definitions, interpretability and computational efficiency.

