### Objectives

To emulate a target trial using UK CF Registry data based on a previously conducted RCT, CF-WISE and assess whether the findings of the emulations are consistent with the results from the CF-WISE trial.To apply the PNUD and sequential trials design to emulate a discontinuation trial, to establish the estimands being targeted under the two designs, compare the results and interpret any differences.

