##### Sequential trials design

The same study period between 1 January 2016 and 30 June 2018 is specified, organised into regularly spaced (eg, monthly) artificial trials within that time period. Individuals are eligible for the first trial if they meet all the eligibility criteria (see *Inclusion and exclusion criteria*) on 1 January 2016. This approach is then applied, with updated covariate data where available (at annual reviews), to every successive new time origin between January 2016 and June 2018.

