##### Sequential trials design

In the sequential trials design, the sequence of emulated ‘trials’ will be constructed and then pooled (ie, stacked) together for the analysis. Adjusted Cox proportional hazards regression models will be used to estimate conditional HRs, including treatment status at the start of each trial and adjusting for the baseline confounders in each trial.

Conditional HRs (adjusted for baseline covariates) from a cause-specific model for pulmonary exacerbation will be presented. We will also obtain estimates of marginal cumulative incidences based on the cause-specific hazard models for pulmonary exacerbation, and for the competing events of death and transplant, followed by empirical standardisation. Marginal risk differences at 6 months will be obtained from the marginal cumulative incidences. Bootstrapping will be used when estimating all 95% CIs.^38^

As in the PNUD, in addition to the ITT estimate, the PP effect will be estimated by censoring individuals when they deviate from their assigned treatment strategy within each artificial trial. IPCW weights will be derived as specified in the PNUD above, but separately in each artificial trial.

See online supplemental material appendix 1 for additional information on estimands, data analysis and analysis of secondary outcomes.

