## Data checks and feasibility analysis

Preliminary inspection of the UKCFR data to address feasibility queries was undertaken. The main objective was to ascertain the number of people registered on the UKCFR who were recorded as discontinuing from ICS in the study period (1 January 2016–30 June 2018). We also ascertained that key variables required for the analysis appear to be reliably recorded.

There were 536 people who discontinued ICS in the study period after at least 90 days of sustained use, before applying the other exclusion criteria (see *Covariates*). ICS start and stop dates appear to have been recorded consistently across the study period. Data on intravenous antibiotic episodes (see *Outcomes*) were also recorded reliably from 2016 onwards with exact dates for the beginning and end of treatment days.

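### The comparison of the two designs (Objective 2) plans no between-design difference with its own uncertainty, and two separate confidence intervals from shared data cannot supply it

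*Protocol article*

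**What the plan says.** All references are to the Protocol article.

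- *Objectives*: the second objective is to apply both designs and "to establish the estimands being targeted under the two designs, compare the results and interpret any differences".
- *Comparison of methods* (under Benchmarking): "we will compare the point estimates and 95% CIs obtained under both designs". It continues: "Discussion and exploration of comparisons between the two study designs will also be undertaken", covering estimands, cohort definitions, interpretability and computing.
- *Benchmarking the index trial*: for the comparison with CF-WISE, the plan goes further and includes "calculating the standardised difference estimate and 95% CI for the difference using bootstrapping".
- *Main analysis*: intervals are bootstrapped in the PNUD, and for the sequential trials design "Bootstrapping will be used when estimating all 95% CIs". No joint bootstrap of the two designs is described.
- *Time periods*, sequential trials design: "The same study period between 1 January 2016 and 30 June 2018 is specified". The inclusion criteria and variables are also common to both designs, and a discontinuer's time zero is the stopping date in both.
- *Causal estimands*: the PNUD targets the ATT. The sequential design is to be used for the ATT as well as an ATE, so that the results can be compared validly.

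**The concern.** The quantity that answers Objective 2 is the difference between the two designs' estimates. The article names the comparison method but attaches no measure of uncertainty to that difference. Each design's interval carries its full sampling error. Where both analyses use much the same people and events, a large part of that error is common and cancels in the difference. The two intervals alone therefore cannot show whether a gap between the estimates is noise or a systematic effect of design.

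The error can go either way. Wide overlapping intervals may be described as consistent when the designs differ systematically. A visible gap between point estimates may equally be interpreted as a design effect when it is chance. The methodological conclusion, which is half of the stated objectives, would then rest on judgement by eye.

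**Working it through.** The article gives no figure for the between-design comparison, so there is none to reproduce. The check asks what two separate intervals can say about the difference.

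**Inputs**

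- Discontinuers: "There were 536 people who discontinued ICS in the study period", before the other exclusions (*Data checks and feasibility analysis*).
- SE of each log HR, s: not in the article; assumed 0.10. For scale, a 6-month risk of 20% gives 536 × 0.20 = 107.2 events. With ten times as many comparator events, s = √(1/107.2 + 1/1072) = 0.101. A risk of 30% gives 160.8 events and s = 0.083. The risks and the tenfold ratio are assumptions.
- Correlation r between the two estimates: not in the article; varied.

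**Formulas** (equal SEs)

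- SE of the difference = s√(2(1−r)).
- A paired 95% interval excludes zero when the difference in log HR exceeds 1.96·s·√(2(1−r)).
- Two separate 95% intervals fail to overlap only when it exceeds 2 × 1.96·s = 3.92s, whatever r is.

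**Ratio of HRs needed at s = 0.10**

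| r | SE of difference | Paired contrast | Non-overlap |
|---|---|---|---|
| 0.5 | 0.100 | exp(0.196) = 1.22 | exp(0.392) = 1.48 |
| 0.7 | 0.077 | exp(0.152) = 1.16 | 1.48 |
| 0.8 | 0.063 | exp(0.124) = 1.13 | 1.48 |
| 0.9 | 0.045 | exp(0.088) = 1.09 | 1.48 |

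At a true difference that the paired contrast detects with 80% power, non-overlap would occur with probability 13% at r = 0.5, 1.2% at 0.7 and 0.03% at 0.8. A softer reading, one estimate lying outside the other's interval, would succeed in 80%, 61% and 38%. All these probabilities apply only if such a reading were used as the criterion.

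**Same two intervals, different answers.** Take an illustrative observed ratio of HRs of 1.10, so ln 1.10 = 0.0953, with s = 0.10 in each design.

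- r = 0.5: exp(0.0953 ± 0.196) gives 0.90 to 1.34, compatible with no difference.
- r = 0.9: exp(0.0953 ± 0.0877) gives 1.01 to 1.20, excluding no difference.

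The separate intervals are identical in both cases. What decides the matter is r, which they do not show.

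**How large might r be?** A simplified simulation ran both designs on the same data: about 505 to 535 discontinuers, 30 monthly trials, an odds-weighted marginal model against a covariate-adjusted stacked model, exponential models in place of Cox, and 150 replicates in each of four scenarios. It gave r of about 0.99, SEs of 0.07 to 0.09 per design, and an SD of the difference of 0.011 to 0.015. This indicates a high correlation under simplified conditions; it is not an estimate for the registry.

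**The case against.** **No overlap rule is stated.** A reader might infer that overlap will be taken as agreement, and hence that a real difference would almost never be recognised. The article does not support this: it sets no decision rule and allows for interpretation. This objection stands. The non-overlap figures are conditional, and the direction of error is open. Nor would an overlap reading amount to treating the designs as independent samples: independence would need a difference of 1.96 × √2 = 2.77 SEs, and non-overlap needs 3.92.

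**The overlap of people is not total.** A reader might take the discontinuers to be identical in the two designs. The article does not say so. Eligibility is reassessed between sequential trials, and a PNUD discontinuer needs comparators in the exposure set. The PNUD also restricts comparators by calendar time and ICS history, whereas the sequential design uses all continuers. Largely the same discontinuers is as far as the text goes, and it is enough for positive correlation.

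**Separate intervals have a proper use.** *Comparison of methods* raises precision in smaller samples as an open question, and the separate intervals address it directly. This stands, and they should be kept.

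**A contrast of the HRs as presented could mislead.** The PNUD HR is marginal, with treatment as the only covariate; the sequential HR is conditional on baseline covariates. They can differ through non-collapsibility alone, and a precise paired contrast could report that as a design effect. This stands and determines which contrast should lead.

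**The detail may lie elsewhere.** Supplemental appendix 1 and any analysis plan are not shown. However, the article itself states how the designs will be compared, and it states a difference with an interval for CF-WISE only. The point is therefore about the stated method, not about detail left out.

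**Conclusion.** The concern holds in limited form. As written, the comparison for Objective 2 provides no uncertainty for the between-design difference, and separate intervals from positively correlated estimates do not provide it. The correlation follows from the shared registry, window, criteria, outcome and discontinuers' time zero.

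The size depends on assumptions the article does not fix. At an SE of 0.10 per design and correlations of 0.5 to 0.9, a paired contrast would distinguish observed ratios of HRs of 1.22 down to 1.09. Reading agreement from overlap, if anyone did so, would need 1.48. Both HRs are assumed to be on one scale for this arithmetic, which the presented HRs are not. The change should be made, but the defect affects the methodological comparison only; the effect estimates within each design and the benchmarking against CF-WISE are untouched.

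**What to change.** In *Comparison of methods*:

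1. Name the lead contrast: the between-design difference in the marginal 6-month risk difference (ITT), with both designs standardised to the ATT, as *Causal estimands* already intends. Both designs already plan marginal cumulative incidences that account for death and transplant.
2. Estimate it by a paired bootstrap: resample persons once per replicate, rebuild the PNUD exposure sets and the sequential trials from that same resample, run both analyses, store the difference, and report it with its 95% CI.
3. Contrast log HRs only if both are put on the same marginal ATT scale. Otherwise present the two HRs with a statement that they differ in kind.
4. Keep the two separate intervals for comparing precision, and say that their overlap is not used to judge agreement.

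The cost is small. Bootstrapping is already planned in both designs, so the addition is shared resamples, a stored difference and some computing time. A log HR contrast would cost more, because the main text plans no marginal HR for the sequential design; the risk-difference contrast does not need one.

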## Data checks and feasibility analysis

Preliminary inspection of the UKCFR data to address feasibility queries was undertaken. The main objective was to ascertain the number of people registered on the UKCFR who were recorded as discontinuing from ICS in the study period (1 January 2016–30 June 2018). We also ascertained that key variables required for the analysis appear to be reliably recorded.

There were 536 people who discontinued ICS in the study period after at least 90 days of sustained use, before applying the other exclusion criteria (see *Covariates*). ICS start and stop dates appear to have been recorded consistently across the study period. Data on intravenous antibiotic episodes (see *Outcomes*) were also recorded reliably from 2016 onwards with exact dates for the beginning and end of treatment days.

## Limitations

A recent study measured the concordance of TTEs and index RCTs and concluded that close replication is possible but may be difficult to achieve, emphasising the need for principled causal study design.^45^ In particular, benchmarking can be challenging given key differences between the index trial and TTE, including that the study populations may differ. In our context, people from higher socioeconomic backgrounds and with less severe disease are more likely to have participated in the index trial,^46^ and the clinical setting in the CF-WISE trial period (2001–2004) may also differ from that in the TTE period (2016–2018).

The study design relies heavily on accuracy of stop and starting dates for ICS in the UKCFR. Under-reporting or delayed reporting of stopping dates may lead to misclassification of discontinuation. Moreover, ICS use is based on a record of the treatment having been prescribed rather than actual use, and so the medication may have been dispensed but not adhered to.

A key limitation is the potential for unmeasured confounding leading to violation of the conditional exchangeability assumption. While statistical methods in the PNUD and sequential trials design will be used to control for differences in the characteristics of treatment groups with respect to measured covariates, some influence of unmeasured confounders may remain. This limitation will be investigated using QBA methods (*Sensitivity analyses*).

Our definition of the primary outcome may lead to misclassification bias as there are differing thresholds for identifying and treating pulmonary exacerbations in clinical practice, and indications for intravenous antibiotics may differ by CF centres and clinical teams.^25 47^ There are, however, previous studies using this definition to investigate treatment effects using UKCFR data. We will perform a sensitivity analysis to check the robustness of conclusions to the definition for the primary outcome (*Sensitivity analyses*).^26^

Another challenge relating to definitions relates to a diagnosis of asthma in people with CF. Asthma is a key covariate in this study due to asthmatic patients being excluded in CF-WISE. The UKCFR captures asthma as reported by the clinical team. This pragmatic definition does not require specific diagnostic criteria, instead relying on this being documented as a known co-morbidity within the patient’s medical records at site. This is a potential limitation in our study.

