### Study design

We will use UKCFR data to conduct an emulation of a target trial based on the CF-WISE trial. This will be done using two study designs: (1) the PNUD and (2) the sequential trials design.^3 17^ The two study designs use distinct but related approaches to making use of observational data and applying statistical analyses to estimate causal effects, with control for measured confounding and time-related biases being at both design and analysis phases.^3 17^ The data used for these emulations will be from 2016 to 2018, chosen intentionally based on data quality and completeness in the UKCFR data and being in the pre-CFTR modulators era. Table 1 specifies the protocol components of the index trial (CF-WISE), the corresponding target trial (hypothetical RCT we would undertake if it were feasible) and how each element of the target trial will be emulated using UKCFR data.

**Table 1 T1:** Specification and emulation of a target trial of deprescribing from inhaled corticosteroids in the UKCFR

Protocol component	CF-WISE (index randomised trial*)	Target trial	Target trial emulation using UKCFR
Eligibility criteria	People diagnosed with CF aged ≥6 years, with FEV _1_≥40% predicted, sustained ICS use ≥3 months. Recruitment period November 2001 and July 2004. Excluded are people who used oral corticosteroids, high-dose ICS or intravenous antibiotics in the 4 weeks prior to treatment assignment.	Same as CF-WISE, except study period is between January 2016 and June 2018. This period reflects a balance between data quality and completeness in UKCFR and prior to the widespread introduction of CFTR modulators.	Prevalent new-user design*:* Same as target trial, except ICS dosage was not recorded. Individuals are eligible for the base cohort (see *Study design*) on the earliest date within the study period that they meet all eligibility criteria. Sequential trials design: Same as target trial, except ICS dosage not recorded. Successive regularly spaced ‘trials’, with eligibility criteria redefined based on most recent data if available.

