Outcomes	Primary: time to first pulmonary exacerbation Secondary: (i) lung function change (FEV_1_ and FVC), (ii) new/unplanned courses of intravenous antibiotics and (iii) rescue bronchodilator usage	Same as CF-WISE	Primary: same as target trial, with different definition for pulmonary exacerbation; defined as a course of hospital or home intravenous antibiotics (see *Outcomes*). Secondary: (i) mean change in FEV_1_% predicted and FVC% predicted. Secondary outcomes (ii) and (iii) will not be assessed due to similarity of UKCFR definitions for intravenous antibiotic courses and pulmonary exacerbation and inability to define rescue bronchodilator use, respectively.
Causal contrasts	Intention-to-treat	Same as CF-WISE	Observational analogue of intention-to-treat and per-protocol
Statistical analysis	For primary outcome, a Cox proportional hazard regression was used. The Wilcoxon rank sum test was used to compare % change in lung function. ORs or relative risks were estimated to compare categorical outcomes (ii and iii). Prespecified subgroup analyses for age, atopic status, dose of ICS, baseline FEV_1_ and *Pseudomonas aeruginosa* infection status.	Same as CF-WISE	Prevalent new-user design: Weighted Cox proportional hazards regression will be used to estimate HRs and 95% CIs. Marginal survival curves and risk difference at 6 months will be estimated. Sequential trials design: Adjusted Cox proportional hazards regression to estimate HRs and 95% CIs. Marginal survival curves and risk difference at 6 months estimated using standardisation. For both designs, intention to treat and per-protocol estimates will be calculated, the latter using inverse probability of censoring weights to account for informative censoring where individuals switch from assigned treatment during follow-up. For information on analysis for secondary outcomes (lung function) see online supplemental material appendix 1 .

* When the target trial is based on an existing RCT this corresponding RCT is termed the reference or index trial. Some aspects of the index trial and target trial may differ because it is not possible to emulate them in observational data, and separating the index and target trials can help to highlight where any differences in findings from the emulated trial compared with the index trial may arise.^48 49^

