#### Prevalent new-user design

In the PNUD, to be included in the base cohort individuals should have a diagnosis of CF, be aged ≥6 years, have a forced expiratory volume in 1 s (FEV _1_)≥40% predicted at most recent annual review, and prescribed ICS for >3 months before the date of ICS discontinuation, for both the discontinuer in each exposure set and their corresponding continuers. Excluded are those who were prescribed oral corticosteroids and/or intravenous antibiotics in the 1 month prior to the ICS discontinuation date, for both the discontinuer in each exposure set and their corresponding continuers. Exclusion of individuals taking higher doses of ICS as specified in the target trial is not possible in the emulated trial as dosage information is unavailable in the UKCFR.

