#### Covariates

In the emulated trials, treatment discontinuation or continuation is not randomised and so measured potential confounders of the relationship between ICS discontinuation and clinical outcomes must be adjusted for to meet the assumption of no unmeasured confounding, a requirement for unbiased causal effect estimation.^30^

Based on a priori clinical expertise, we will adjust for the following covariates at baseline: age, sex, genotype, body mass index z-score, CF-related diabetes, FEV_1_% predicted, home and hospital intravenous antibiotics, hospital admissions, *P. aeruginosa* infection, *Burkholderia* infection, non-tuberculous mycobacteria infection, allergic bronchopulmonary aspergillosis, pancreatic insufficiency, liver disease, inhaled bronchodilator use (captured as a separate variable to ICS), asthmatic status (as a proxy to atopic status specified in CF-WISE), inhaled antibiotic use and mucoactive therapy use (hypertonic saline, mannitol and DNase).

For both the PNUD and sequential trials design, these covariates will be recorded at the nearest annual review date preceding time zero. Since ICS stopping dates may occur at any point between successive annual reviews, stopping dates will occur at various time intervals following baseline annual review across individuals. Therefore, time from previous annual review (in months) to time zero for both the discontinuers and continuers will be adjusted for in the analyses.

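### The protocol contradicts itself on whether CF-WISE excluded people with asthma; if it did, the benchmark compares populations that adjustment for asthma does not align

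*Protocol article*

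**What the plan says.** **On CF-WISE.** In the Limitations section, the paragraph on defining asthma states: "Asthma is a key covariate in this study due to asthmatic patients being excluded in CF-WISE". The CF-WISE column of Table 1 (Study design) gives the exclusions as: "Excluded are people who used oral corticosteroids, high-dose ICS or intravenous antibiotics in the 4 weeks prior to treatment assignment". Asthma is not among them.

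**On the target trial and the emulation.** Table 1 gives target trial eligibility as "Same as CF-WISE, except study period is between January 2016 and June 2018" and prevalent new-user eligibility as "Same as target trial, except ICS dosage was not recorded"; the sequential trials entry declares the same single departure. Under Inclusion and exclusion criteria, the exclusion for the prevalent new-user design reads "Excluded are those who were prescribed oral corticosteroids and/or intravenous antibiotics in the 1 month prior to the ICS discontinuation date", and the sequential trials design takes over the same criteria with reassessment over time. Neither design excludes asthma.

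**On how asthma is used.** It is a baseline adjustment variable, described under Covariates as "asthmatic status (as a proxy to atopic status specified in CF-WISE". It is also a subgroup: "We will investigate discontinuation effects by asthmatic status", subject to adequate sample size.

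**On benchmarking.** The section Benchmarking the index trial asks whether the direction of the HR agrees with CF-WISE and whether the emulated effect falls in the CF-WISE 95% CI, computes a standardised difference, and asks whether the clinical conclusion would be the same. No restriction by asthma is mentioned. The criteria are to be read with attention to how well the populations align.

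**The concern.** Table 1 exists to show where index trial, target trial and emulation differ, so that a disagreement in results can be traced to its source. One section of the article asserts an eligibility difference that this table does not contain. A reader who relies on Table 1 would not know that asthma might be a point of misalignment.

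If the exclusion is real, the Limitations sentence draws an insufficient consequence from it. It treats the exclusion as a reason to make asthma a covariate. Weighting or regression on asthma balances discontinuers and continuers within the cohort. It does not change whom the effect is averaged over: the ATT or ATE described under Causal estimands still includes people with asthma. The Subgroup analyses section supplies the reason to expect effect modification, since it describes ICS as an established treatment in asthma and reports the caution of the CF-WISE authors about that group.

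The first objective is consistency with CF-WISE. A difference in asthma mix could then look like disagreement with the trial, or could offset a genuine disagreement.

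**Working it through.** **1. Text comparison.**

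| Place | Asthma in eligibility |
|---|---|
| Limitations | Excluded from CF-WISE |
| Table 1, CF-WISE | No exclusion listed |
| Table 1, target trial | As CF-WISE except period |
| Table 1, emulation | As target trial except ICS dosage |
| Inclusion and exclusion criteria, both designs | No exclusion |

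The first two rows cannot both be complete and correct. Both are in the article, so condensation from a fuller protocol does not explain the conflict.

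**2. The benchmark figure.** The section on the index trial gives HR 1.07 (0.68 to 1.70) for fluticasone versus placebo.
- SE of the log HR: ln(1.70/0.68)/(2 × 1.96) = 0.916/3.92 = 0.234.
- Geometric midpoint: √(0.68 × 1.70) = 1.075. The CI rebuilt from 1.07 is 0.68 to 1.69. The figure is internally consistent.
- Inverted to discontinue versus continue: 1/1.07 = 0.93, with limits 1/1.70 = 0.59 and 1/0.68 = 1.47.

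**3. Illustration of the effect of asthma mix.** The asthma share p and the stopping HR in asthma are assumptions; the documents give neither. Suppose people without asthma reproduce CF-WISE exactly (0.935 before rounding), and that p is also their share of the statistical information. Then approximately

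whole-cohort HR = exp[(1 − p) × ln 0.935 + p × ln(HR in asthma)]

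| Share p | HR in asthma | Whole-cohort HR |
|---|---|---|
| 20% | 1.3 | 1.00 |
| 20% | 2.0 | 1.09 |
| 30% | 1.5 | 1.08 |
| 40% | 1.3 | 1.07 |
| 40% | 2.0 | 1.27 |

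**4. Against the benchmarking criteria.**
- Direction: 0.93 is below 1. All the values except the 1.00 corner are above 1, although the matching population agrees perfectly.
- CI inclusion: every value lies within 0.59 to 1.47. To leave the interval, the HR in asthma would have to be about 2.9 at a 40% share: (ln 1.47 − 0.6 × ln 0.935)/0.4 = 1.07, and exp(1.07) ≈ 2.9. At a 20% share it would have to be about 9.
- Standardised difference at the extreme, ignoring sampling error in the emulation: (ln 1.27 − ln 0.935)/0.234 ≈ 1.3.

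**5. The opposite case.** Suppose the HR without asthma were 0.55, outside the interval. Pooled with 1.5 in asthma at a 10% share, the result is exp(0.9 × ln 0.55 + 0.1 × ln 1.5) = 0.61, inside the interval. The mix can hide a disagreement as well as create one.

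**The case against.** **The documents cannot say which statement is right.** This stands. The Limitations sentence is one clause in a paragraph about diagnostic definition, and the reported caution about people with asthma neither confirms nor refutes an exclusion. A reader might infer that Table 1 is the faulty text and that the cohort without asthma must replace the whole cohort as the benchmark. The documents do not support that: if Table 1 is right, such a restriction would create the mismatch it is meant to cure.

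**The plan already has safeguards.** This stands in part. Benchmarking is to be read in light of population alignment, the Limitations section concedes that populations may differ, and estimates by asthma status are planned. But the population differences it names are socioeconomic background, severity and clinical era. Asthma is never named as an eligibility departure, and the subgroup is conditional and not tied to benchmarking.

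**The size is assumed and modest.** This stands. CI inclusion holds throughout the illustrated range. The trial's own direction is undetermined, so a reversal around 0.93 is fragile under any perturbation and is not specific evidence about asthma.

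**Restriction is imperfect.** This stands. By the protocol's own account, the registry asthma record needs no specific diagnostic criteria, and restriction would cut into the 536 discontinuers counted before the other exclusions.

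**The outcome.** A reader might extend the point to endpoints and ask for the emulated intravenous-antibiotic outcome to be benchmarked against the CF-WISE secondary outcome on antibiotic courses. The plan states that this secondary outcome "will not be assessed due to similarity of UKCFR definitions for intravenous antibiotic courses and pulmonary exacerbation", discloses the different primary definition, and plans sensitivity analyses on it. The article shows no CF-WISE estimate for that outcome, so the extension is not supported here.

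**Conclusion.** The contradiction over CF-WISE eligibility is on the face of the document and needs correction whichever statement proves right. What follows for the analysis is conditional. If the exclusion is confirmed, the whole-cohort estimate and CF-WISE refer to different populations, adjustment for asthma does not close the gap, and Table 1 omits a departure that bears on the first objective.

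On the assumed values, the whole-cohort stopping HR moves from 0.93 to about 1.00–1.27. This exposes the direction criterion and the standardised difference but not CI inclusion. The range rests on assumed shares and hazard ratios, on people without asthma matching CF-WISE exactly, and on log-linear pooling. It shows what could happen, not what is likely. A reader might conclude that the benchmark verdict would be wrong as planned; the documents support only that it could not be interpreted cleanly. This should be fixed before results are seen, but it does not invalidate the design.

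**What to change.** 1. Check the index trial's own eligibility criteria and make Table 1 and the Limitations section agree.
2. If the exclusion is confirmed, add it to the CF-WISE column of Table 1, carry it through or declare it as a departure in the target trial and emulation columns, and prespecify in both designs the estimate in people without recorded asthma as a benchmark comparison. Report it beside the whole-cohort estimate under Benchmarking the index trial, and do not leave it only as a subgroup conditional on sample size. Keep the whole cohort as the answer for the broader population. State that the registry asthma record may not reproduce the trial's definition.
3. If the exclusion is not confirmed, correct the Limitations sentence; no restricted benchmark is then needed on this ground.

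The cost is a change of wording and one restricted run of analyses already planned by asthma status. The restricted estimate loses precision according to the asthma share, which should be reported. CF-WISE's own SE of 0.234 on the log scale already limits how sharp the comparison can be.
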